## Abstract

**Background:**

Structured education programmes for individuals with Type 1 diabetes have become a recognised means of delivering the knowledge and skills necessary for optimal self-management of the condition. The Dose Adjustment for Normal Eating (DAFNE) programme has been shown to improve biomedical (HbA_1c _and rates of severe hypoglycaemia) and psychosocial outcomes for up to 12 months following course delivery. The optimal way to support DAFNE graduates and maintain the benefits of the programme has not been established. We aimed to compare 2 different methods of follow-up of DAFNE graduates in a pragmatic clinical trial delivered in busy diabetes clinics on the island of Ireland.

**Methods:**

Six participating centres were cluster randomised to deliver either group follow-up or a return to traditional one-to-one clinic visits. In the intervention arm group follow-up was delivered at 6 and 12 months post DAFNE training according to a curriculum developed for the study. In the control arm patients were seen individually in diabetes clinics as part of routine care. Study outcomes included HbA_1c _levels, self-reported rates of severe hypoglycaemia, body weight and measures of diabetes wellbeing and quality of life. These were measured at 6, 12 and 18 months after recruitment. Generalisability (external validity) was maximised by recruiting study participants from existing DAFNE waiting lists in each centre, by using broad inclusion criteria (including HbA_1c _values less than 13 percent with no lower limit) and by using existing clinic staff to deliver the training and follow-up. Internal validity and treatment fidelity were maximised by quality assuring the training of all DAFNE educators, by external peer review of the group follow-up sessions and by striving for full attendance at follow-up visits. Assays of HbA_1c _were undertaken in a central laboratory.

**Discussion:**

This pragmatic clinical trial evaluating group follow-up after a structured education programme has been designed to have broad generalisability. The results should inform how best to manage the well educated patient with Type 1 diabetes in the real world of clinical practice

**Trial registration:**

Current Controlled Trials ISRCTN79759174

## Background

Type 1 diabetes is a challenging condition to manage. Once diagnosed it requires active patient involvement in self-management of lifestyle issues including diet, physical activity and stress reduction. Most patients are expected to self-administer insulin subcutaneously several times a day and monitor its effects through frequent (and painful) self-monitoring of capillary blood glucose levels. Even in motivated patients it can be difficult to avoid day-to-day fluctuations in blood glucose levels resulting in symptomatic hyper- or hypoglycaemia. Although the risk of chronic microvascular complications of diabetes can be reduced by maintaining good glycaemic control, in an individual patient there is no guarantee that their genetic predisposition will not result in premature impairment of vital organs including the eyes, kidneys and peripheral nerves. Worry about complications and the fear of hypoglycaemia are significant burdens for many people living with the disease [1].

In Ireland and the UK systems for delivering care to individuals with type 1 diabetes have traditionally been very hospital and healthcare professional oriented. Typically a patient will be offered 3-4 visits per year to a hospital outpatient clinic or Diabetes Centre. During these visits a doctor and/or nurse will review certain clinical (e.g., weight, blood pressure) and laboratory (e.g., glycated haemoglobin, lipid levels) parameters and may establish targets for the patient to achieve. The patient's self-monitoring of blood glucose data may be reviewed although this does not always happen [2]. During at least one of these visits annual screening for microvascular complications will be undertaken. Traditionally, education to support self-management has not been a major focus of the diabetes clinic visit. If it is delivered the education is often undertaken in an ad hoc manner and without reference to a clear education plan. Perhaps not surprisingly, when formally assessed through clinical practice audit, outcomes associated with this traditional method of diabetes care delivery are not good. This is true both for adults and children with Type 1 diabetes [3,4] where average levels of HbA_1c _of 8.6 to over 9.5 percent have been reported.

The concept of therapeutic patient education was first introduced to medical practice through the pioneering work of Jean-Phillipe Assal, a Swiss doctor and educationalist [5]. It aims to provide a more holistic approach to patient care while ensuring that the knowledge, skills and attitudes necessary to achieve effective self-management (or mastery) of the long-term condition are delivered to the patient. In the case of Type 1 diabetes a German diabetologist, Michael Berger, and his group in Düsseldorf first operationalised this concept through the development of an "Insulin Treatment and Teaching Programme" in the late 1970's. They demonstrated through randomised controlled trials that this approach was associated with improved glycaemic control and no increase in rates of severe hypoglycaemia [6]. The approach is now widespread throughout Germany [7]. In the late 1990's a group of UK diabetes care professionals observed the Düsseldorf programme and adapted it for delivery in an outpatient setting in 3 UK centres. The Dose Adjustment for Normal Eating (or DAFNE) programme is a 5 day structured education programme covering all aspects of living with diabetes with an emphasis on the key skill of estimating carbohydrate intake and matching insulin to food [8]. Using a waiting list controlled design among individuals with poorly controlled diabetes the UK group showed significant improvement in HbA_1c _levels at 6 months but a diminution of this effect by 12 months. Rates of severe hypoglycaemia did not increase with the improvement in glycaemic control while patient-reported quality of life improved significantly [9].

The DAFNE approach to diabetes care delivery was greeted with considerable enthusiasm by patients [10], healthcare professionals [11] and policy makers [12]. Since publication of the results of the DAFNE trial a further 74 diabetes teams in the UK and Ireland have undertaken training of their staff to deliver the programme [8]. Preliminary reports of audit data from a number of these DAFNE centres suggest that improvements in glycaemic control and psychosocial measures of wellbeing similar to the DAFNE trial are being achieved in routine practice [13]. However, unlike the situation in Germany where sustained benefit has been reported [7], long-term data from the UK indicate a diminution of the HbA_1c _improvement [14]. This raises the issue of how best to support the long-term needs of a patient who has been through DAFNE training. This is the central question being addressed in the Irish DAFNE Study. The hypothesis on which the study is based is that group follow-up of DAFNE graduates is superior to individual follow-up. The philosophy of the DAFNE programme is grounded in Therapeutic Patient Education Theory [15]. The group education approach incorporating theories of adult learning has been used in structured education programmes for people with Type 2 diabetes, such as DESMOND [16] and ROMEO [17]. This paper describes the design, setting, interventions and outcomes of the Irish DAFNE Study, an 18 month cluster randomised trial of self-management support among patients with Type 1 diabetes.

### Irish DAFNE Study Objectives

1. To develop a new model of ongoing care for DAFNE graduates based on structured group follow-up and peer support

2. To undertake an evaluation of this new model of care (group follow-up of DAFNE graduates) comparing it with "usual care", i.e., a return to the standard one-to-one clinic visits following DAFNE training.

## Methods

### Design

The Irish DAFNE Study is a pragmatic, open, cluster randomised, parallel group trial comparing 2 different methods of follow-up of patients with Type 1 diabetes who have received the 5-day DAFNE programme in participating Irish hospitals. The study design and patient recruitment are represented in Figure 1, using the CONSORT flow diagram. The CONSORT approach will be followed in reporting the results of this clinical trial [18].

**Figure 1 F1:**
[figure not shown]
**Flow of centres and participants throughout the trial**.

Ethical approval was obtained from the Research Ethics Committee of National University of Ireland, Galway (06/MAY/04), from the Research Ethics Committee of Galway University Hospitals (CA 19), from COREC Northern Ireland (06/NIR01/126) and from the local research ethics committee of each participating hospital. The decision to obtain ethical approval from each participating centre was based on the Irish legislature's interpretation of European Union clinical trials legislation. Had the intervention been a medicinal product (rather than an educational package) this requirement would have been waived in favour of approval from a single Research Ethics Committee.

Written informed consent was obtained from all participants in the Irish DAFNE Study after they had sufficient time to consider the Patient Information Sheet and had any questions relating to their participation answered by study personnel.

### Setting and Centre Recruitment

There are approximately 35 hospitals in the Republic of Ireland delivering outpatient care to individuals with Type 1 diabetes. The equivalent number for Northern Ireland is approximately 11 hospitals. In 2005 when this study was conceptualised only 2 of these 46 hospitals was offering the DAFNE programme to its patients. An additional 5 diabetes teams were in the process of receiving DAFNE training or had plans to do so in the near future. One of these centres was based in primary care and the lead doctor declined an invitation to participate in the study. The remaining 6 hospital-based teams agreed to combine their efforts into delivering a programme of research, the Irish DAFNE study. Although random selection of diabetes centres would have been preferable this was not an option because of the considerable commitment required on the part of a diabetes team to become a DAFNE Centre (see Figure 2).

**Figure 2 F2:**
[figure not shown]
**Becoming a DAFNE Centre**. DNS - Diabetes Nurse Specialist; DEP - DAFNE Educator Programme; DDP - DAFNE Doctor Programme.

### Randomisation and Patient Recruitment

In the study we used a cluster randomisation with the unit of randomisation being the participating DAFNE centre. There are 6 participating centres in this study and it was anticipated that each cluster would have approximately 75 participants each. We felt that DAFNE educators would not be able to separate the 2 approaches to follow-up if they were expected to deliver both. By randomising centres to deliver one or other method of follow-up we hoped to minimise or avoid contamination between the two arms of the study. The process of randomisation of centres was undertaken by a statistician not involved in the study and who was blind to the identity of the hospitals being randomised. The randomisation was done using a computer-generated table of random numbers.

Prior to the study each of the participating DAFNE centres used a similar approach to filling DAFNE courses. A waiting list was maintained of individuals with Type 1 diabetes attending the centre who had expressed an interest in receiving DAFNE training. Using this list, groups of approximately 50 patients were invited to attend a recruitment evening in which the DAFNE course was described and members of the DAFNE team were available to answer questions. A brief description of the study aims and objectives was included in the material presented at the recruitment evening. Individuals were asked to consider participating in the study but were not required to give an answer at the recruitment evening. Following the recruitment evening approximately 6 DAFNE courses (each comprising 8 participants) would be filled. Prior to the week of DAFNE training, individuals were invited to attend a pre-course assessment visit. During this visit a DAFNE educator would make sure that the individual met the inclusion criteria for the study. Informed consent was generally obtained at this visit and baseline study questionnaires were given to the patient.

Study Inclusion criteria:

1. At least 18 years of age at recruitment

2. Diagnosed with type 1 diabetes for at least one year

3. Attending the adult diabetes clinic in one of the participating centres

4. The ability to speak and read English

5. A willingness to monitor blood sugar levels at regular intervals

6. A willingness to transition to a basal/bolus insulin regimen prior to DAFNE training (if not already on such a regimen)

7. A glycosylated haemoglobin (HbA_1c_) level below 13 percent at recruitment.

Study Exclusion criteria:

1. Diagnosed with type 2 diabetes

2. Attending a paediatric clinic

3. Pregnant or planning a pregnancy in the next 2 years

4. The presence of advanced diabetes complications (e.g. kidney failure with serum creatinine >250 μmol/L)

5. Serious co-morbidity likely to interfere with study participation (assessed by the study centre's physician)

6. Previous DAFNE training or current use of a continuous subcutaneous insulin infusion pump

### DAFNE and Study Interventions

The DAFNE course is delivered over 5 consecutive days and involves 38 hours of structured education in all aspects of managing Type 1 diabetes. The education is delivered by a Diabetes Specialist Nurse, Dietitian and Doctor all of whom have undergone training in delivery of the DAFNE curriculum. Figure 2 illustrates the rigorous training process that a diabetes team has to go through to become a DAFNE centre. One of the real strengths of the DAFNE programme is the quality assurance that is incorporated into its delivery. DAFNE educators regularly undergo peer review (both within their centre and via external peer review) to ensure they are maintaining a consistent high standard of course delivery. This means that the basic package (the DAFNE course) delivered in each of the participating DAFNE centres was uniform and standardised to a level appropriate for a research study. Details of the individual sessions that comprise the DAFNE course are available on the DAFNE Collaborative website [8] and all resource literature is available to DAFNE graduates via the DAFNE Online website [19]. Participants in the intervention arm centres also receive sessions on goal setting and action planning as part of the DAFNE week.

Following DAFNE course delivery patients are invited back as a group for a 6 week return visit with the educators (nurse and dietitian) who delivered their original course. This was considered an essential component of the basic DAFNE course and was not removed from either arm of the study. After this 6 week return visit participants in the usual care arm of the study are offered return visits to the diabetes clinic at 6, 12 and 18 months post DAFNE training. This reflects usual care in Irish DAFNE centres prior to the study. The protocol does not stipulate what issues are covered in these visits. The only stipulation is that participants should not be seen in a group setting. It is recognised that attempts are likely to be made to have patients in this arm of the study seen by the doctor, nurse and/or dietitian involved in their original DAFNE training. However, patients may also be seen by diabetes team members not trained in DAFNE.

Participants in the intervention arm of the study are also seen at 6, 12 and 18 months. The 6 and 12 month visits are organised as group education sessions and build on the concepts of goal setting and action planning introduced during the original DAFNE course. A follow-up curriculum was developed to guide DAFNE educators involved in delivering these sessions and specific training in the delivery of this curriculum was given to all intervention arm DAFNE educators. Groups are encouraged to determine their own priorities and select from a range of DAFNE self-management skills review topics designed specifically for these follow-up sessions. The role of the DAFNE educator is to achieve a blend of a patient-centred and curriculum-centred approach to the session. Follow-up curriculum topics include HbA_1c _and targets, diary keeping and self-monitoring, principles of dose adjustment, carbohydrate calculation, hypoglycaemic management, exercise and physical activity, alcohol and sick day rules. An example of a typical timetable for a group follow-up session is outlined in Table 1. Where DAFNE graduates are unwilling or unable to participate in a follow-up session with their original group they are offered a follow-up session with a different DAFNE group from that centre. Every effort is made to avoid delivering follow-up on a one-to-one basis in this arm of the study. In keeping with an emphasis on quality assurance an external peer review of the delivery of one 6 month follow-up session in each of the 3 intervention arm centres will be undertaken during the study.

**Table 1 T1:** Typical timetable used during the intervention follow-up sessions

09:30	Welcome
09:40	HbA_1c _results, review of blood sugar and targets

10:10	Quiz to identify 3 areas the group would like to focus on (patient-centred approach)

10:20	Curriculum used to guide group-led discussion of identified topics

12:10	Goal setting and action planning

12:30	Close

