### Statistical Considerations

#### Sample Size

We used a sample size calculator designed for cluster randomised trials [25]. We based the sample size calculation on an anticipated HbA_1c _difference between the 2 arms of the study of 0.5 percent from month 6 onwards. This came from the observation in the UK study that DAFNE training led to a 1.0 percent drop in HbA_1c _at 6 months but reverted to 0.5 percent by 12 months [9]. Our study hypothesis is that group follow-up will be able to maintain the benefit out to 18 months. Unlike the UK DAFNE Study patients were not excluded with baseline HbA_1c _below 7.5 percent. Based on a standard deviation of HbA_1c _of 1.2 and an intra-class correlation co-efficient of 0.05 we estimated that 450 patients would be required to detect a 0.5 percent difference with 90 percent power.

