The design of the Irish DAFNE Study presented several challenges to the study steering group. Although guided by the CONSORT statement on the conduct and reporting of high quality randomised controlled trials [18], it became clear that this was not a straightforward randomised controlled trial. The Irish DAFNE Study is evaluating a non-pharmacological treatment intervention using a cluster randomised design and has several features of a pragmatic trial. Therefore, 3 of the extensions of the CONSORT statement are relevant to our study and its description [35].

A number of design features help with the study's internal validity (i.e., they minimise bias). These include the uniform approach to DAFNE training across centres and the incorporation of peer review and quality assurance into the delivery of the programme. The central measurement of HbA_1c_, one of the main study outcomes, is also a strength of the design. In terms of external validity (or generalisability) the study also has strengths including the recruitment of participants from existing waiting lists in each centre, the use of broad inclusion criteria for potential participants and the delivery of the intervention by diabetes clinic personnel. A potential weakness (in terms of generalisability) is the fact that the results could be seen as relevant only to centres delivering structured group education. However, including DAFNE and other similar programmes there are now in the region of 150 Diabetes Centres across the UK and Ireland involved in this type of activity.

Most importantly perhaps, the results of the Irish DAFNE Study will be relevant to individuals living with Type 1 diabetes. At a time when more and more diabetes studies are funded by pharmaceutical companies with the intention of getting a new product to market or identifying a new indication for an existing drug, it is important not to forget about interventions and outcomes that are important to patients. A recent review of ongoing diabetes studies (identified through clinical trial registries) found that only 18 percent included patient important outcomes as their primary outcome [36]. When primary or secondary outcomes were examined the number including patient-important outcomes increased to 46 percent.

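### The trial compares a package (goal-setting sessions in the DAFNE week plus group follow-up) with usual care, but the hypothesis credits group follow-up alone

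*Protocol article*

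**What the plan says.** The Background section gives the hypothesis: "group follow-up of DAFNE graduates is superior to individual follow-up". The Design section describes the trial as "comparing 2 different methods of follow-up of patients with Type 1 diabetes who have received the 5-day DAFNE programme". The second objective takes the new model of care to be group follow-up and sets it against a return to one-to-one clinic visits. The abstract likewise describes the intervention arm only by its group sessions at 6 and 12 months.

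Under DAFNE and Study Interventions, the article says that "the basic package (the DAFNE course) delivered in each of the participating DAFNE centres was uniform and standardised". The same paragraph ends: "Participants in the intervention arm centres also receive sessions on goal setting and action planning as part of the DAFNE week". The account of the intervention arm then explains that the 6- and 12-month group sessions build on the goal setting and action planning introduced in the course, and Table 1 closes the typical session with that activity.

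The Discussion, listing features that protect internal validity, says: "These include the uniform approach to DAFNE training across centres".

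**The concern.** If the arms differ only in follow-up, an 18-month difference can be credited to follow-up. Here they also differ in the content of the course week, about 6 months before the first study group session. The primary outcome runs from baseline, so any effect of the added sessions is part of the primary contrast.

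This affects the use of the result. The Discussion expects the trial to inform policy on diabetes education. A centre that kept a standard DAFNE week and added only group follow-up would not be delivering what was tested, although the hypothesis as worded would suggest that it was.

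**Working it through.** **1. The statements side by side**

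| Place in the protocol article | What differs between the arms |
|---|---|
| Background (hypothesis), Objective 2, Design, abstract | Method of follow-up only |
| DAFNE and Study Interventions, basic course | Nothing: uniform in all centres |
| DAFNE and Study Interventions, end of the same paragraph | Added goal-setting and action-planning sessions in intervention centres |
| DAFNE and Study Interventions, follow-up | Curriculum-based group sessions at 6 and 12 months against individual visits |
| Discussion (internal validity) | Nothing in DAFNE training |

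**2. What the randomised contrast contains**

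Let g = 1 if the added sessions are given in the course week, and f = 1 if follow-up is in groups. Let Y(g, f) be the mean HbA1c change to 18 months. The trial observes Y(1,1) and Y(0,0). Their difference splits exactly as

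Y(1,1) − Y(0,0) = [Y(1,0) − Y(0,0)] + [Y(1,1) − Y(1,0)].

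The first bracket is the effect of the added sessions. The second is the effect of group follow-up given those sessions. Both need Y(1,0), which no arm supplies. An effect of group follow-up after a standard course would need Y(0,1), which is also absent. The sum is estimated validly; its parts are not.

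**3. Timing**

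The primary outcome is HbA1c change from baseline to 18 months (Outcomes and Measurement). Baseline questionnaires are given at the pre-course visit (Randomisation and Patient Recruitment). The article does not date the baseline HbA1c sample; a pre-course sample is inferred. On that reading, the effect of the added sessions lies inside the measured change.

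**4. Can the existing visits separate the components?**

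Inputs: 6 centres of about 75, so 3 centres and 225 participants per arm; SD 1.2; ICC 0.05; planned difference 0.5.

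- Design effect: 1 + (75 − 1) × 0.05 = 4.7.
- SE of an unadjusted arm difference at one visit: 1.2 × √(2 × 4.7 / 225) = 0.245.
- 95% half-width, normal: 1.96 × 0.245 = 0.48.
- 95% half-width, t with 6 − 2 = 4 df: 2.776 × 0.245 = 0.68.

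The half-width is about as large as the whole planned effect, or larger. A 6-month difference near zero would rule out little, and a clear one could reflect chance differences between three centres and three others. Baseline adjustment would narrow the interval by an amount that the article does not let one calculate.

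For the arm difference in change from 6 to 18 months, the within-person correlation is not given. If the SD of that change were also 1.2 (a correlation of 0.5) and its ICC also 0.05, the same half-widths would apply. The greater difficulty does not depend on precision: skills taught in the course may persist, or may act through the group sessions that build on them, so the later change mixes both components.

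**5. The stated sample size**

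The 450 enters above only as 6 × 75. As a power calculation it does not reproduce: with an assumed two-sided 5% level, 122 per arm before clustering gives 244 × 4.7 ≈ 1,147. That is a separate matter, and nothing in this point depends on it.

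**The case against.** The strongest defence is that the trial declares itself pragmatic, and a pragmatic trial may test a package. The first objective is to develop a new model of ongoing care, and the course sessions plainly prepare participants for the follow-up curriculum. The follow-up visits themselves also differ in curriculum, educator training and format, so no single ingredient was going to be isolated. This stands: the package contrast is legitimate and unharmed. It does not rescue the wording, because the hypothesis, second objective and design statement do not name that package.

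A second defence concerns uniformity. The basic course can be read as the core that both arms share, with a disclosed addition in one arm. That is coherent, so a reader who infers a flat contradiction from "delivered in each of the participating DAFNE centres was uniform and standardised to a level appropriate for a research study" goes too far. The Discussion carries no such qualifier, however, and lists uniform training as a protection against bias; a qualifier is needed there.

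Three stronger readings are tempting and are not supported:

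- **That the comparison is invalid.** It is a valid estimate of a package effect.
- **That the 6-month difference measures the added sessions and the 6-to-18-month change measures follow-up.** The precision and carry-over arguments above rule this out.
- **That the sample-size text, which expects a "difference between the 2 arms of the study of 0.5 percent from month 6 onwards", assumes an effect before any study group session.** Its rationale (a 1.0 drop at 6 months reverting to 0.5 by 12 months) does imply no difference at month 6. But the phrase can mean divergence after that visit, and neither the sample size nor the 18-month primary analysis depends on a month-6 difference.

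**Conclusion.** The point holds as one of attribution. The article states arm-specific course content, then words its hypothesis, second objective and design as if only follow-up differed. An 18-month difference would support the package, not group follow-up alone.

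The share due to the added sessions is unknown and could be small. The conclusion rests on the stated course content, on the two-arm design and on a pre-course baseline HbA1c, the last being inferred. The precision figures further assume that the article's SD and ICC apply at 6 months, with equal centres of 75.

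**What to change.** Make these wording changes:

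1. Restate the hypothesis, the second objective, the design statement and the conclusion to be drawn as: DAFNE with goal-setting and action-planning sessions plus curriculum-based group follow-up, against standard DAFNE plus individual follow-up.
2. Qualify the uniformity statements, under DAFNE and Study Interventions and in the Discussion, as applying to the core course shared by both arms.
3. Optionally, report the 6-month HbA1c difference and the 6-to-18-month change by arm, with intervals that respect the six centres. Label both as exploratory description, and label neither as the effect of follow-up.

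No new data are needed, since HbA1c is already measured at each visit (Table 2). The cost is a narrower claim: the trial could recommend the package, but could not say that group follow-up after a standard course would achieve the same.
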